#### **4.5 Early Termination Visit**

If a patient prematurely terminates the study, a complete final examination as detailed in Section 4.2 is to be performed at the time of withdrawal. Furthermore the blood sample for determination of the neutralizing anti-ancrod antibody should be taken on day 30 ( $\pm$  one week) if possible.

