#### 4.6. General Presentation of Summaries and Analysis

All study data will be presented in individual patient data listings. Data will be sorted by treatment, patient number, and visit. Where appropriate, the listings will include derived variables as per Section 4.3.

Each statistical table will contain a reference to the related patient data listing.

All study variables will first be analyzed in a descriptive way. Descriptive statistics will be displayed by treatment group (and overall if applicable) as follows:

- Continuous variables will be described using the number of non-missing values, arithmetic mean, standard deviation, minimum value, median, and maximum value ('summary statistics')
- Categorical variables will be presented by the absolute frequency (n) and the relative percentage (%) for each observed modality, whereas missing values will be displayed as own category ('frequency table').

Statistical tables will show results for each treatment group. For baseline and background variables, an additional 'Overall' column will be included, but not for efficacy and safety variables.

In general, the analysis of safety data will be based on the Safety set (SFS). The analysis of efficacy data will be based primarily on the Full analysis set (FAS), while alternative summary tables on efficacy variables will be done on the Per protocol set (PPS) as sensitivity analysis. Each analysis population will contain patients of both treatment groups in approximately a 2:1 ratio.

Usually, all patients within a given analysis population will be considered for analysis; descriptive by-visit analyses will be based upon only those patients who did not terminate the study prior to a given visit. Each table will display the total number of patients per treatment group (and overall, if applicable).

Further specifications regarding the layout of end-of-text tables and listings are given in Appendix 13.4 of this SAP. A list of all statistical tables and listings to be produced can be found in Appendices 13.2 and 13.3. These overviews also indicate the analysis population(s) for which a respective parameter will be evaluated. Moreover, the generation of mock TFLs is addressed in Section 13.7.

Any figures/graphics produced must be legible after been copied in black even if the original version is colored.

The layout of in-text tables for a subsequent report is covered in Appendix 13.6.

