#### 5.3. Handling of Dropouts and Missing Data

A screening failure is a patient having signed informed consent but discontinuing before being randomized. Such patients are not kept in the database.

Dropout patients are not explicitly referenced in the study protocol. However, the following definition is provided in this SAP:

- Patients randomized who either discontinue the study prematurely or are withdrawn from study by the investigator before the planned study termination are assessed as **dropouts**.

Dropout patients are not substituted. To compensate for dropouts, a 12 % dropout rate was used in the sample size determination.

Dropout patients will be evaluated like any other patient terminating the study regularly while accounting for missing data. The FAS includes dropout patients.

Missing values will usually be shown as missing in patient data listings. If there is the need to show data imputations, imputed values are flagged appropriately.

For the statistical analysis of efficacy variables, the LOCF (last observation carried forward) method will be applied to impute missing Visit 5 values, i.e, the baseline value will be carried forward. Missing values for Visit 6 or Visit 7 will not be replaced as these visits are far beyond treatment stop.

Regarding PTA, a missing PTA threshold value for a given frequency at Visit 5 is replaced by the respective preceding value available at Screening. Imputations will not use values of the other ear (left/right) or of the other conduction type (air/bone). If a baseline value for a given frequency is missing, the frequency will be excluded from statistical analysis of the respective patient.

Regarding the statistical evaluation of background and safety variables, missing values will not be replaced or imputed; they will be handled as missing by displaying an own category in frequency tables.

However, missing data, outliers and other spurious or implausible data are discussed in the BDRM prior to unblinding the database.

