## 10. Safety Analyses

All safety parameters will be evaluated for all patients treated (Safety set, SFS). All statistical tables will show data by treatment group but not for overall. If not indicated otherwise, only descriptive statistics will apply.

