# The coagulation parameter fibrinogen is analyzed as efficacy variable.

\* Categorical analysis with 'Positive' and 'Negative'.

° Before CRF version 4.1, the parameter titled "Blood in urine".

For each numeric parameter, the baseline value will be determined as the latest value before or at Day 1. Then, values at Baseline and Day 8 as well as the absolute change will be given in a summary table by treatment group.

Moreover, a shift analysis will be presented for each numeric parameter. In this, the categorized change from Baseline to Day 8 will be displayed. Possible categories are 'Below the LLN', 'Within the normal range', and 'Above the ULN', according to the flag variable introduced in Section 4.3.

Categorical parameters will be presented in frequency tables by visit (Baseline, Day 8).

The number of patients with clinically relevant laboratory values will be given by parameter in a frequency table.

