#### **10.5. General Physical Examination**

A physical examination is performed at Screening (Visit 1) to document the patient's medical history and at Day 8 (Visit 5) to document changes since Screening.

Separately for each body system listed in the CRF, the categories at Screening ('Not done', 'Normal', 'Abnormal') and at Day 8 ('Not done', 'No change', 'Change') will be given in a frequency table. Any specifications for abnormality and change will be presented in a patient data listing.

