#### **10.7. Vital Signs**

Vital sign parameters (body weight, systolic and diastolic blood pressure, and pulse rate) are recorded for Screening (Visit 1) and Day 8 (Visit 5). All data will be listed. Values of above four parameters for Screening and Day 8 and the absolute change from Screening to Day 8 will be displayed in a summary table.

In addition, a frequency table will be provided for pulse pattern ('Regular', 'Not regular') by visit.

Vital signs will also be tabulated in shift tables providing the number of patients whose values are within or outside the normal ranges. The following normal ranges (orientating at WHO definitions) will be used:

- BMI: 18.5 to <25.0 kg/m^2
- Systolic blood pressure: 105 to <140 mmHg
- Diastolic blood pressure: 65 to <90 mmHg
- Pulse rate: 60 to <85 beats per minute.

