| Order in subject data listings                                       | Randomized patients by Treatment group, Patient number and Visit (if applicable)                                                                                                                                                                                                                                                                                                                                                                                                                              |
| Labels and order of treatment groups                                 | First 'Ancrod', then 'Placebo', then 'Overall'                                                                                                                                                                                                                                                                                                                                                                                                                                                                |
| Labels and order of visits                                           | Visit 1 (Screening)
Visit 2 (Day 2)
Visit 3 (Day 4)
Visit 4 (Day 6)
Visit 5 (Day 8)
Visit 6 (Day 30)
Visit 7 (Day 90)                                                                                                                                                                                                                                                                                                                                                                       |
| Labels for descriptive summary statistics for continuous variables   | Use n, Mean, SD, Min, Median, Max (instead of number of non-missing values, arithmetic mean, standard deviation, minimum value, median, and maximum value)                                                                                                                                                                                                                                                                                                                                                    |

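### For a patient who leaves the study before Visit 5, the SAP gives the required withdrawal examination no place in the post-baseline safety summaries

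*Combined protocol and SAP*

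**What the plan says.** Protocol 4.5 states that, on premature termination, "a complete final examination as detailed in Section 4.2 is to be performed at the time of withdrawal"; Sections 5.1.4 and 9.3 repeat the requirement. The only full examination list in Section 4.2 is the one for Day 8: physical and ear examination, vital signs, coagulation, hematology, chemistry and urinalysis. Protocol 8.1.1 names an early withdrawal visit alongside Days 1, 8, 30 and 90.

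The SAP handles post-baseline safety data as follows.

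- Section 4.6: "descriptive by-visit analyses will be based upon only those patients who did not terminate the study prior to a given visit".
- Section 10.3, numeric laboratory data: "values at Baseline and Day 8 as well as the absolute change will be given in a summary table by treatment group". The shift and categorical laboratory tables also use Baseline and Day 8.
- Section 10.5, physical examination: done at Screening and "at Day 8 (Visit 5) to document changes since Screening".
- Section 10.6, ear examination: the safety items are those collected at Screening and Day 8.
- Section 10.7, vital signs: "the absolute change from Screening to Day 8 will be displayed in a summary table".
- Section 5.3: "Regarding the statistical evaluation of background and safety variables, missing values will not be replaced or imputed".
- Section 13.4: the visit labels run from Visit 1 to Visit 7 and end "Visit 5 (Day 8) Visit 6 (Day 30) Visit 7 (Day 90". The schedule in 13.1 has no early-termination column, and the windows in 4.3 cover Visits 1 to 7 only.

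Section 10 sets the population: "All safety parameters will be evaluated for all patients treated (Safety set, SFS").

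**The concern.** The protocol collects a complete set of post-dose safety data from every patient who withdraws, yet the SAP does not say where it goes. Read as written, a patient who leaves between the first dose and Visit 5 is outside the Day 8 summaries, and nothing is imputed in place of the missing value.

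Leaving may be related to harm: Protocol 5.1.4 and 9.3 list adverse events and laboratory abnormalities among the reasons for withdrawal. Post-dose summaries restricted to those who stayed could then understate, for example, falls in hemoglobin, blood in urine or changes in clotting tests. SAP 2 expects only a few more than 30 evaluable patients, so one or two such patients can move a summary visibly.

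**Working it through.** **1. Trace one patient.** Take a patient in the Safety Set who leaves the study on Day 4 and has the withdrawal examination that day.

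| Output | Post-dose time point in the SAP | What the patient contributes |
|---|---|---|
| Laboratory change, shift and categorical (14.3.4.1 to 14.3.4.3) | Day 8 | No post-dose value |
| Physical examination (14.3.5) | Day 8 | No post-dose value |
| Ear examination (14.3.6) | Day 8 | No post-dose value |
| Vital signs (14.3.7.1 to 14.3.7.3) | Day 8 | No post-dose value |
| Clinically relevant laboratory values (14.3.4.4) | No visit limit stated | Possibly counted |
| Fibrinogen change to Day 2 (14.2.4.2) | Day 2 | Counted, if sampled |
| Adverse event tables (14.3.1 and 14.3.2 series) | Not by visit | Counted |
| Listings | All data | Shown |

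The gap arises from SAP 4.6 together with the table definitions in SAP 10.3 and 10.5 to 10.7. Section 13.4 only confirms it.

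**2. Dropout allowance.** Inputs: 87 evaluable patients (Protocol 10.1, SAP 3.5) and 12% dropout (SAP 5.3). N/(1 − d) = 87/0.88 = 98.9, rounded up to 99, which reproduces the plan. The allowance is 99 − 87 = 12 patients: 66 − 58 = 8 on ancrod and 33 − 29 = 4 on placebo. It covers dropout over the whole study. The documents do not say how many would leave before Day 8.

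**3. Number affected.** Assume that 3% to 12% leave before Day 8, the upper end being the whole allowance.

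- At the planned size: 99 × 0.03 = 3.0 to 99 × 0.12 = 11.9 patients.
- At an assumed final size of 33 to 40: 33 × 0.03 = 1.0 to 40 × 0.12 = 4.8 patients, both arms together.

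**4. What it could do to a summary.** The counts and values here are assumptions. With 36 patients at 2:1, 24 receive ancrod.

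- *One leaver.* The leaver and 2 of the 23 others have blood in urine at their last examination. The Day 8 table shows 2/23 = 8.7%; among all examined it is 3/24 = 12.5%.
- *Three leavers* (0.12 × 24 = 2.9, near the upper end). Two of the leavers and 2 of the 21 others are positive. The table shows 2/21 = 9.5%, against 4/24 = 16.7%. If the leavers are instead displayed as missing under SAP 5.3, it shows 2/24 = 8.3%. In both displays their positive results go uncounted.
- *Hemoglobin, three leavers.* If each lost 2 g/dL and the others nothing, the Day 8 mean change is 0.0; with the leavers it is (3 × −2 + 21 × 0)/24 = −0.25 g/dL.
- *No leavers.* No difference.

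**The case against.** **Silence is not exclusion.** The withdrawal examination is defined through Section 4.2, so a site might record it on the Visit 5 pages. SAP 4.3 flags a Visit 5 outside Days 7 to 9 and sends it to the blind data review rather than dropping it, and an examination on Day 7 can fall within the window. Part of SAP 4.3 is also missing from the text reviewed, so a mapping rule there is unlikely but cannot be ruled out. This stands as a qualification. It leaves the outcome to recording practice, which a plan should settle.

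**A reader might infer that these patients disappear from the safety report.** They do not. Screening values stay in the tables, all data are listed, and n and missing categories make a shortfall visible. Bleeding enters the adverse event tables, including events leading to discontinuation. The cover is incomplete, though. Protocol 9.1.1 keeps fibrinogen, TT, PT and aPTT out of the abnormal laboratory values that count as adverse events, and SAP 10.3 summarizes TT, PT and aPTT at Baseline and Day 8 only.

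**A reader might infer that stopping injections for bleeding or low fibrinogen removes a patient.** The protocol separates the two. Bleeding signs are reasons to interrupt drug, and after a low Day 2 fibrinogen all other study activities continue (Protocol 3.1 and 4.2). Only leaving the study matters here. The documents give no figure showing that this is more frequent on ancrod.

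**A reader might see a contradiction with SAP 10.** That sentence names the analysis population; using the data available at each visit within it is ordinary practice. These tables are also descriptive, with no planned tests.

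**Conclusion.** The gap is real and narrow. If the SAP is followed as written, a patient who leaves the study before Visit 5 contributes no post-dose laboratory, physical, ear or vital-sign value to the arm summaries, although the protocol required those data. The exception is an examination that happens to be recorded as Visit 5.

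The size rests on assumed early exit rates and an assumed final sample: probably a few patients at most, and nothing at all if nobody leaves before Day 8. The direction of any distortion depends on why patients leave, which is not known. The illustrations in the working show what could happen and are not estimates. The point does not concern imputation of the hearing endpoint. It is worth settling before unblinding, because the choice of how to use these records should not be made with the treatment arms known.

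**What to change.** In SAP 4.6 and 10, with a matching label in 13.4, add an 'End of treatment' row or column to Tables 14.3.4.1 to 14.3.4.3, 14.3.5, 14.3.6 and 14.3.7.1 to 14.3.7.3. It uses the Visit 5 record or, if Visit 5 was not done, the early-termination examination performed on or before Day 9. State that the by-visit restriction in 4.6 does not apply to this row. Keep the Day 8 column as planned, and show the number of early-termination records per arm. If a mapping rule already exists in SAP 4.3, cite it instead.

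The cost is SAP wording and one mapping step in the analysis datasets. No new data are needed, since the protocol already requires the examination. The blind data review minutes serve as an addendum to the SAP (SAP 1), so the rule could also be fixed there. The drawback is that the added row mixes examination days for a few patients; keeping the Day 8 column alongside lets the reader see how much that matters.

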### 13.5. Documentation of Statistical Methods

[To be included in Appendix 16.1.9 of the CSR]

For the primary efficacy variable, confirmative testing is performed with the aim to show superiority in favor of the treatment with ancred over placebo, applying a two-sided 5 % significance level. All other variables are exploratively compared between treatment groups.

For quantitative efficacy variables, statistical testing to compare both treatment groups is done using an analysis of covariance (ANCOVA) based on the generalized linear model. Qualitative parameters are analyzed with Fisher's exact test (2×2-tables) or the Freeman-Halton test (tables larger than 2×2).

### 13.6. Table of 'In Text' TFLs

The generation of a clinical study report (CSR) or a statistical report is not contracted. Beside the end-of-text TFLs listed in Sections 13.2 and 13.3, separate specific in-text tables will be generated by YYY upon request only.

### 13.7. Shells for TFLs

For the general layout of end-of-text tables and listings, see Section 13.4. Shells for TFLs (so-called 'mock TFLs') will not be generated.

### 13.8. Raw Statistical Output

[To be included in Appendix 16.1.9 of the CSR]

Raw output of all applied SAS procedures will be stored in study-specific folders. It is planned to hand over SAS raw outputs referring to the primary efficacy analysis. For all other variables, only the agreed end-of-text tables that are based on the raw output will be compiled.

### 13.9. Data Deliverables

The following deliverables will be handed over to NORDMARK after study completion:

- A document containing all end-of-text tables and figures
- A document containing all patient data listings
- A document containing the raw output from SAS procedures.
